## Abstract

**Background:**

Depression and chronic diseases are frequently comorbid public health problems. However, clinical guidelines often fail to consider comorbidities. This study protocol describes a cluster randomized trial (CRT) aimed to compare the effectiveness of a collaborative, computer-assisted, psycho-educational intervention versus enhanced usual care (EUC) in the treatment of depressed patients with hypertension and/or diabetes in primary care clinics (PCC) in Santiago, Chile.

**Methods:**

Two-arm, single-blind, CRT carried out at two municipalities in Santiago, Chile. Eight PCC will be randomly assigned (1:1 ratio within each municipality, 4 PCC in each municipality) to the INTERVENTION or EUC. A total of 360 depressed patients, aged at least 18 years, with Patient Health Questionnaire-9 Item [PHQ-9] scores ≥15, and enrolled in the Cardiovascular Health Program at the participating PCC. Patients with alcohol/substance abuse; current treatment for depression, bipolar disorder, or psychosis; illiteracy; severe impairment; and resident in long-term care facilities, will be excluded. Patients in both arms will be invited to use the Web page of the project, which includes basic health education information. Patients in the INTERVENTION will receive eight sessions of a computer-assisted, psycho-educational intervention delivered by trained therapists, a structured telephone calls to monitor progress, and usual medical care for chronic diseases. Therapists will receive biweekly and monthly supervision by psychologist and psychiatrist, respectively. A monthly meeting will be held between the PCC team and a member of the research team to ensure continuity of care. Patients in EUC will receive depression treatment according to clinical guidelines and usual medical care for chronic diseases. Outcome assessments will be conducted at 3, 6, and 12 months after enrollment. The primary outcome will be depression improvement at 6 months, defined as ≥50% reduction in baseline PHQ-9 scores. Intention-to-treat analyses will be performed.

**Discussion:**

This study will be one of the first to provide evidence for the effectiveness of a collaborative, computer-assisted, psycho-educational intervention for depressed patients with chronic disease at primary care in a Latin American country.

**Trial registration:**

retrospectively registered in ClinicalTrials.gov, first posted: November 3, 2020, under identifier: NCT04613076.

## Background

### Background and rationale

According to the Global Health Estimates by the World Health Organization (WHO), non-communicable diseases, such as cardiovascular diseases and diabetes, accounted for 68.4% of total deaths worldwide in 2015 [1]. Up to date global burden of disease data also reveals that depressive disorders are the single largest cause of global disability, leading to considerable losses in health and functioning and contributing to nearly 800,000 deaths by suicide per year [2, 3]. Population ageing means that cardiovascular diseases and diabetes are becoming more prevalent, while depression might further limit the capacities of this ever increasing older workforce [3, 4]. Moreover, studies have revealed that depression comorbid with medical conditions is the rule rather than the exception, as up to two thirds of the depressed subjects were diagnosed with physical health comorbidities in a Scottish country-wide primary care study [5], with the disease cluster of cardio-metabolic conditions and depression being one of the most common multimorbidity patterns throughout clinical settings according to a systematic review [6]. Comorbid depression has been associated with incremental decrements in health [7], prolonged hospital stays and higher chance of rehospitalization [8], lower treatment adherence [9], and increased risk of mortality [10, 11]. Thus, endorsement of the statement “no health without mental health” should readily translate into evidence-based clinical practice guidelines that consider physical and mental health comorbidities [12].

During the past decades, the Collaborative Care Model (CCM) has proven successful in integrating behavioral health services into primary care [13]. Under this model of care, mental health care is provided in a coordinated fashion with the support of a case manager, supervision by a consultant psychiatrist, and the use of patient-reported outcome measures to tailor clinical decision-making to patients’ needs [13]. Studies have consistently reported that the CCM improves depressive symptoms, health-related quality of life, and social functioning of depressed individuals, with no net increase in health care costs [14]. CCM is effective in the treatment of people with depression alone or with comorbid medical conditions [15]; and it might be beneficial for glycemic and blood pressure control in depressed patients with poorly controlled chronic diseases [16]. Additionally, the current literature on CCM has identified some essential components for the implementation of effective integrated disease management programs, such as the inclusion of cognitive-behavioral therapy and problem-solving techniques [17], or motivational interviewing interventions [18], self-help resources delivered through the Internet or computer-based applications [19–21], timely case manager follow-up within the first 4 weeks to increase clinical attention and patient engagement [22], and psychiatric consultation for those patients not achieving improvement after 2 months [22]. However, evidence and experts’ recommendations for effective CCM usage come mainly from developed countries [14], and may not wholly apply to developing nations.

Chile is a developing, high-income Latin American country that has made major advances over the last 30 years in the management of medical and mental health conditions. For instance, Chilean governments have made a strong commitment to promote healthy living and prevent chronic diseases through community-based health programs for people covered by public health insurance [23], and have developed a comprehensive community-based mental health care network, integrating mental health into primary care throughout the country [24]. Moreover, based on the success of a randomized controlled trial to treat depression in low-income women in primary care clinics in Chile’s capital city, Santiago [25], a stepped-care program for depression management, which combined medical and psychosocial interventions, was implemented in 2001 and rapidly scaled-up across primary care facilities in the country [24]. Complementarily, the Chilean Regime of Explicit Health Guarantees, a comprehensive health reform enacted in 2005, mandated guarantees of access, quality, opportunity, and financial coverage by public and private health insurance for priority diseases and conditions [24]. Hypertension, type II diabetes, and depressive disorders were part of the first set of 56 priority diseases, ensuring access to an extensive, evidence-based basket of benefits which are structured according to clinical practice guidelines, informing quality, cost-effective primary care practice.

Despite substantial progress towards universal health access and coverage in Chile [26], especially for depression [24], effective coverage for hypertension and diabetes remains particularly low compared to infectious diseases or maternal and child care [26]. Furthermore, according to the Chilean National Health Survey 2016–2017, there has been a sustained increase in the proportion of people with diabetes [27], while no variation has been observed for the population prevalence of depression [28]. These figures may be attributable to the minimum impact of preventive interventions, as evidenced by the prevalence of cardiovascular risk factors [26], or to important inconsistencies in the provision of treatment, as in the case of depression, where diagnostic inaccuracy and treatment dropout are the main problems in the management of depressed primary care patients [29, 30]. Moreover, while 80% percent of depressed patients at primary care clinics had comorbidity [31], and depressive symptoms are common among hypertensive patients [32], the Chilean clinical practice guidelines for cardio-metabolic and depressive disorders do not consider their common comorbidity in primary care settings. Thus, the country’s epidemiological and health services profile, characterized by a tendency towards ageing, highly prevalent non-communicable diseases, and mental disorders, motivates the urgent search for effective primary care interventions integrating a mental health component in the management of chronic diseases.

## Objectives

### General objective

To compare the effectiveness of a collaborative, computer-assisted, psycho-educational intervention, called “Me cuido y me siento mejor” [I Take Care of Myself and Feel Better], versus enhanced usual care in the treatment of depressed patients with hypertension and/or diabetes in primary care clinics in Santiago, Chile.

### Specific objectives

To compare the proportion of patients with improvement in depressive symptoms treated with the “Me cuido y me siento mejor” intervention versus enhanced usual care in primary care clinics.To compare the proportion of patients recovered from depression treated with the “Me cuido y me siento mejor” intervention versus enhanced usual care in primary care clinics.To compare the levels of health-related quality of life and social problem-solving skills in patients treated with the “Me cuido y me siento mejor” intervention versus enhanced usual care in primary care clinics.To compare the values of blood pressure and/or glycosylated hemoglobin of patients treated with the “Me cuido y me siento mejor” intervention versus enhanced usual care in primary care clinics.To compare treatment acceptability of the “Me cuido y me siento mejor” intervention versus enhanced usual care in primary care clinics.

### Hypotheses

The proportion of patients with improvement in depressive symptoms will be 23% higher in the “Me cuido y me siento mejor” primary care clinics compared to the enhanced usual care primary care clinics, at 6-month follow-up.The proportion of patients recovered from depression would be higher in the “Me cuido y me siento mejor” compared to the enhanced usual care primary care clinics, at 6-month follow-up.Patients in the “Me cuido y me siento mejor” primary care clinics would have better social problem-solving skills and health-related quality of life than patients in the enhanced usual care primary care clinics, at 6-month follow-up.Patients in the “Me cuido y me siento mejor” primary care clinics would have lower blood pressure and improved glucose regulation than patients in the enhanced usual care primary care clinics, at 6-month follow-up.Patients in the “Me cuido y me siento mejor” primary care clinics would report higher treatment acceptability than patients in the enhanced usual care primary care clinics, at 6-month follow-up.

## Methods: participants, interventions, and outcomes

### Study setting

Eight primary care clinics located in two low-to-middle income urban municipalities belonging to the Greater Santiago Metropolitan Area, Chile.

### Eligibility criteria

#### Primary care clinics

*Inclusion criteria:*
Located in urban municipalities belonging to the Greater Santiago Metropolitan Area, Chile.Have implemented a Cardiovascular Health Program and a Depression Program.Have higher than the median population of patients enrolled in the Cardiovascular Health Program among all primary care clinics in the Greater Santiago Metropolitan Area.

### Trial design

Multicenter, parallel-group, two-arm, superiority, cluster randomized trial with 1:1 allocation ratio.

#### Trial participants

*Inclusion criteria:*
Age 18 or older.Enrolled in the Cardiovascular Health Program (i.e. currently receiving treatment for diabetes and/or hypertension) at the study primary care clinics.Patient Health Questionnaire-9 Item (PHQ-9) score ≥ 15.Signed or verbal informed consent.

*Exclusion criteria:*
Functional illiteracy (i.e., patients unable to read and comprehend written information, such as the study questionnaires or written/verbal informed consent).Significant visual and/or auditive impairments (i.e., such as those imposing a serious difficulty to respond the study questionnaires or written/verbal informed consent).Pregnancy or breastfeeding.Cognitive impairment – ineligible patients would give a negative answer to questions “What year is it?” and “Where are we (place/address)?”.In treatment for bipolar and/or psychotic disorder.Current psychological treatment for depression.High risk of developing alcohol/substance abuse problems, according to an Alcohol, Smoking and Substance Involvement Screening Test (ASSIST) score ≥ 27 [33].

#### Who will take informed consent?

Trained recruiters from the trial will contact potential participants for assessment of the initial eligibility criteria for the study. During the evaluation process, recruiters will explain general aspects of the trial to potential participants and will obtain written (or verbal) informed consent from them.

#### Additional consent provisions for collection and use of participant data and biological specimens

Not applicable.

### Interventions

#### Explanation for the choice of comparators

Currently, in Chile, the standards for the management of depression in primary care have been set in the Clinical Guidelines for the Treatment of Depression, issued by the Chilean Ministry of Health [34]. This document summarizes the best evidence available and is periodically updated by a group of local experts. The target population of the Clinical Guidelines for the Treatment of Depression is people aged 15 years or more. Its aims are to guide practitioners in the active detection and integral diagnosis of the pathology while also offering evidence-based recommendations for timely, efficient, and cost-effective depression treatment [34]. The Clinical Guidelines for the Treatment of Depression incorporates decision-making algorithms in which primary care plays a relevant role, enhancing primary care team’s capacities to manage cases of mild, moderate, and severe depression [34]. Furthermore, the Regime of Explicit Health Care Guarantees, establishes a set of guarantees and rights for people with public or private health insurance [35], offering a comprehensive basket of health benefits according to depression severity. In this context, usual care for depression is the reference comparator in Chile [34]. In the present trial, usual care has been complemented with online access to information about depression, diabetes and hypertension, and healthy lifestyles for the participants.

#### Intervention description

Patients in the primary care clinics assigned to the intervention and to the comparator will have access to the project’s website, which will be populated with information about the project’s aims, the research team, and contact data, along with educational material related to depression, diabetes and hypertension, and healthy lifestyles.

#### Active arm

“Me cuido y me siento mejor” is a multicomponent, collaborative, computer-assisted, psycho-educational intervention for the management of depressive symptoms in primary care patients with diabetes and/or hypertension. Patients in the primary care clinics assigned to the intervention will receive:
A computer-assisted, psycho-educational intervention, delivered in-person –or remotely if this is not possible– by trained therapists participating in the trial, at the selected primary care clinics. Eight individual sessions will be held in total, each lasting 45 min. Sessions will be held weekly at first (4 sessions), followed by 4 monthly sessions. The intervention manual will ensure standardized implementation of each session. The manual carefully details the aims, activities, necessary materials, and possible conversations with the patient in each session. The therapists participating in the trial will deliver this intervention with the support of a laptop computer to display slides or videos. This intervention will combine education about health issues (depression, diabetes, and hypertension), basic elements of motivational interviewing, and cognitive-behavioral techniques to involve the patients in the management of their own health issues, encourage behavioral activation, improve problem-solving skills, and modify negative thoughts. The first two sessions, based on health education and motivational interviewing, will actively involve the patients in managing their health issues and will establish a link between depression and chronic diseases, specifying their impact on the patients’ quality of life. Also, a personalized care plan will be developed. The patients will receive support materials such as calendars and a blackboard-type care plan. Sessions three and four will address negative thoughts and problem-solving techniques. The fifth session will incorporate elements of behavioral activation, while the sixth will pay closer attention to thinking errors. In all sessions, the patients’ progress in their care plan will be reviewed. The last two sessions (reinforcement sessions) will elaborate on the associations between the topics covered in each session and will feature the closing activities. The therapists will record information about the topics covered in the sessions in the electronic health records of the participating primary care clinics. The therapists will all be psychologists. Their training will consist in a 12-h induction about the basics of the intervention. This training program will include teaching sessions, role playing, and knowledge tests, which will be in charge of the research team. The therapists will participate in a biweekly supervision by a psychologist from the research team to solve logistical problems and issues with treatment integrity.Telephone monitoring will be in charge of a social worker participating in the trial. Monitoring calls lasting 5 to 10 min will be made during the first 12 weeks of the intervention, once per week, in order to observe the patients’ clinical evolution, the medical care received, and their use of antidepressants and possible collateral effects, while also encouraging adherence to the medical and psycho-educational treatment. The social worker in charge of telephone monitoring, who has a long experience in managing cases in clinical trials for depression treatment, will have a standardized form for recording information.A psychiatrist from the research team will review the social worker’s caseload to formulate treatment recommendations and solve health care problems affecting the patients throughout the study. In addition, the psychiatrist will monthly supervise the study therapists to assist them in the management of the most severe cases and in the collaboration with routine primary care.Once per month, a member of the research team will meet with the teams from the participating primary care clinics. These meetings will be aimed at integrating the mental health care provided by the study therapists with the usual medical care for chronic diseases provided in the cardiovascular health program of each primary care clinic, to ensure continuity of care.Usual medical care for chronic diseases, according to the Cardiovascular Health Program.

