## Outcomes

### Primary outcome

#### Depression improvement

Defined as a 50% reduction in a participant’s Patient Health Questionnaire-9 Item (PHQ-9) score compared to the baseline [36]. The summary measure for each group will be the percentage of participants who respond to their depression treatment at 6-month follow-up. Even though the primary outcome is taken at 6-month follow-up, this measure will also be reported at 3- and 12-month follow-up.

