### Secondary outcomes

#### Depression recovery

Defined as a change in a patient’s depressive status from an initial score above the cutoff (PHQ-9 ≥ 10) and a follow-up score below this reference value (PHQ-9 < 10). The summary measure for each group will be the percentage of participants who respond to their depression treatment at 3-, 6-, and 12-month follow-up.

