#### Methods in analysis to handle protocol non-adherence and any statistical methods to handle missing data

All analyses will be performed according to the principle of intention-to-treat (ITT), which means that all participants are included in the analysis according to the group that were randomly allocated, regardless of the treatment received. Complementarily, per-protocol analyses will be conducted. This group of analyses will include patients who have received at least 85% of the total number of interventions scheduled in the protocol.

In clinical trials, missing data are the rule, not an exception. Therefore, the specialized literature reports the superiority of modern imputation methods (i.e. multiple imputation [MI]) compared to other analysis methods (e.g. complete-case analysis [CCA]) [50]. In the present trial, we will estimate the mechanism of missingness. If found to be pertinent, we will apply the MI method following the procedures described by Enders, Keller, and Levy [51], and Bartlett, Seaman, White, and Carpenter [52], in their extension for the management of grouped data in Blimp 1.1 [51, 53]. These procedures make it possible to manage random slopes, categorical and nominal variables, the disaggregation of inter- and intra-subject effects, and incomplete level 2 variables [51]. The data analysis and combination of the sets of imputed data will be conducted with Stata 14 [49], adjusting the regression coefficients and standard errors according to the combination rules developed by Rubin [54].

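### As worded, the 85% per-protocol rule would make any 3-month per-protocol analysis depend partly on sessions held after the 3-month outcome

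*Protocol article*

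**What the plan says.** The Active arm section of the protocol article sets the number of sessions, "Eight individual sessions will be held in total, each lasting 45 min", and their spacing, "Sessions will be held weekly at first (4 sessions), followed by 4 monthly sessions". It adds telephone monitoring: "Monitoring calls lasting 5 to 10 min will be made during the first 12 weeks of the intervention, once per week". The Methods part of the Abstract counts the 3-, 6- and 12-month assessments from enrollment.

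The section on protocol non-adherence and missing data makes intention to treat the principle for all analyses and then adds: "Complementarily, per-protocol analyses will be conducted". The set for these is "patients who have received at least 85% of the total number of interventions scheduled in the protocol". The denominator is the whole schedule. No visit is named, and nothing confines the count to contacts due before the outcome being analysed.

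The primary time point is 6 months, but under Depression improvement "this measure will also be reported at 3- and 12-month follow-up". Depression recovery is summarised as the percentage of participants "who respond to their depression treatment at 3-, 6-, and 12-month follow-up". The other secondary outcomes also have a 3-month assessment.

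**The concern.** An adherence set for an outcome should be fixed by what happened up to that outcome. Here one cut, taken over the full schedule, would serve every visit, and part of that schedule lies after the 3-month assessment. A patient's place in a 3-month per-protocol set could then depend on sessions attended or missed in months 4 and 5.

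If having improved by month 3 makes a patient more likely, or less likely, to attend those last sessions, membership depends on the outcome itself. A difference between the arms could then appear at month 3 with no treatment effect. The direction cannot be predicted: improved patients may stay because they are engaged, or stop because they feel better. The protocol also has events that can end attendance after month 3. The section on discontinuing or modifying interventions interrupts them on hospitalization for physical worsening, and participants may withdraw.

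**Working it through.** The protocol gives no figure for how much of the schedule falls before month 3, so there is none to reproduce. The check builds it from the stated schedule.

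**Inputs.** Eight sessions, four weekly then four monthly, and 12 weekly calls (Active arm). Threshold 85% of the total (protocol non-adherence and missing data). Assessments at 3, 6 and 12 months from enrollment (Abstract). Control response 27% (Sample size). The day of session 1 relative to enrollment is not stated, so it is varied.

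**Step 1, the bar in sessions.** 0.85 × 8 = 6.8, so seven are needed (6/8 = 75%; 7/8 = 87.5%).

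**Step 2, sessions due by month 3.** Three months = 3 × 30.4375 / 7 = 13.0 weeks. Session 5 is placed one month after session 4.

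| Month length | Session 1, weeks after enrollment | Session weeks | Due by week 13.0 |
|---|---|---|---|
| 30.4 days | 0 | 0, 1, 2, 3, 7.3, 11.7, 16.0, 20.4 | 6 |
| 30.4 days | 1 | 1, 2, 3, 4, 8.3, 12.7, 17.0, 21.4 | 6 |
| 30.4 days | 2 | 2, 3, 4, 5, 9.3, 13.7, 18.0, 22.4 | 5 |
| 28 days | 0 | 0, 1, 2, 3, 7, 11, 15, 19 | 6 |
| 28 days | 3 | 3, 4, 5, 6, 10, 14, 18, 22 | 5 |

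At most six sessions precede the assessment, one short of the bar.

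**Step 3, whose membership is still open at month 3 (sessions only, six due).**
- Attended 6 of 6: needs one of sessions 7 and 8.
- Attended 5 of 6: needs both.
- Attended 4 or fewer: can reach at most 4 + 2 = 6, so is already out.

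**Step 4, if the calls also count.** Contacts: 8 + 12 = 20. Bar: 0.85 × 20 = 17. Due by month 3: up to 6 + 12 = 18 (90%).
- 17 or 18 received: already in.
- 16: needs one of the last two sessions.
- 15: needs both.
- 14 or fewer: at most 14 + 2 = 16, so already out.

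**Step 5, month 6.** Session 8 falls 3 + 4 × 4.35 = 20.4 weeks after session 1. Six months is 26.1 weeks. All eight sessions are therefore due before the 6-month assessment if session 1 is held within 26.1 − 20.4 = 5.7 weeks of enrollment. With a start up to three weeks after enrollment, the last session is at about week 23.

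**Step 6, how far selection on response can move a per-protocol figure.** With response r, and with a and b the proportions of responders and non-responders who reach the cut, the response in the selected set is r·a / [r·a + (1 − r)·b]. Take r = 0.27 in both arms (no effect) and assumed values of a and b:
- a = 0.80, b = 0.60: 0.216 / (0.216 + 0.438) = 33.0%, a false gain of 6 points.
- a = 0.75, b = 0.65: 0.2025 / (0.2025 + 0.4745) = 29.9%, a false gain of 3 points.
- a = 0.60, b = 0.80: 0.162 / (0.162 + 0.584) = 21.7%, a false loss of 5 points.

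Here a and b cover attendance over the whole schedule, before and after month 3, and the comparison is with an unselected 27% in the control arm. The results show total per-protocol selection, not the part due to timing.

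**The case against.** The strongest reply is that the protocol never says a per-protocol analysis will be run at 3 months. It says only that such analyses will be done, and the choice of visits could be settled in an analysis plan that is not shown. This stands as a limit: the 3-month analysis is inferred from a rule without a visit restriction together with outcomes reported at 3 months. It does not remove the point, because the threshold and its denominator are stated, and applied as written they reach past month 3.

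Three further objections also narrow the claim.

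- **Sessions or contacts.** The rule counts interventions, and the calls may be among them. A patient with at least 17 of the 18 contacts due by month 3 then already qualifies, and later attendance matters only for those still short of the bar.
- **Early misses.** A reader might infer that sessions 7 and 8 decide membership for everyone. They do not: on a session count, two misses among the first six already exclude a patient, before the outcome is measured.
- **Size.** A reader might take the 3- to 6-point shifts as the bias from this timing fault. The documents do not support that. The attendance rates are assumed, the same rates give the same shifts at month 6, and the comparison leaves the control arm unselected. They are upper-end examples of what per-protocol selection as a whole can do.

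One more reading of the schedule is possible. If the first monthly session came one week after session 4, and session 1 were held within about a week of enrollment, seven sessions could fit by month 3 (for example weeks 0, 1, 2, 3, 4, 8.3, 12.7). That is not the plain sense of the schedule. Even then the eighth session comes later (week 17.0) and still counts towards the 85%.

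**Conclusion.** The point holds as a minor one. Applied as written, the 85% rule would make a 3-month per-protocol estimate condition partly on attendance after the outcome. On a session count, no active patient can have met the bar by the 3-month assessment, and membership is still open for every patient with at most one miss among the first six. With calls included, it is open only for those still short of 17 at month 3. The direction of the bias is unknown, and the part due to timing cannot be quantified from the protocol.

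This rests on session 5 following session 4 by a month, on session 1 coming at or after enrollment, and on the per-protocol analyses extending to month 3.

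It would be wrong to infer that the trial's main result is at risk. Intention-to-treat results at every visit do not use the rule. The primary outcome is at 6 months, by which time all eight sessions are due if treatment starts within about five weeks of enrollment, so the 6- and 12-month per-protocol analyses do not share this fault.

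**What to change.** Change one sentence in the section on protocol non-adherence and missing data, in one of two ways:

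1. Define per-protocol adherence separately for each assessment, from the contacts due before that assessment; or
2. Restrict the per-protocol analyses to the 6- and 12-month outcomes and report 3-month results by intention to treat only.

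The sentence should also say whether the monitoring calls count, since the 3-month position depends on it. The session schedule need not change.

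The first option changes the denominator at month 3. Keeping 85% there would require all six sessions due (0.85 × 6 = 5.1) or 16 of 18 contacts (0.85 × 18 = 15.3). The second option gives up the 3-month per-protocol table and is the simpler of the two. The first needs session and call dates. The section on strategies to improve adherence says that the therapists and the social worker record each session, but it does not mention dates, so their availability is an assumption to confirm.

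Neither option removes the general selection bias of a per-protocol comparison, in which attendance before the outcome may also be related to response.
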